## 2. Materials and Methods

### 2.1. Study Design

The WISE experimental RCT consists of three components embedded into a smartphone app: (1) a remote HIIT program with video sessions; (2) an interface that includes health information; (3) an activity monitoring tool. The study will be a three-center, randomized (1:1), controlled, parallel-group trial with a six-month intervention period. Young women will be recruited from the communities at three study sites in Spain (University of Valencia, Valencia), Serbia (University Nikola Tesla, Belgrade) and Italy (SPORTLAB, Parma). This study protocol will be reported in accordance with the Standard Protocol Items: Recommendations for Interventional Trials (SPIRIT) guidelines [30], and will follow the CONSORT (Consolidated Standards for Reporting Trials) guidelines for the transparent reporting of parallel group randomized trials [31]. To gain a comprehensive understanding of the study design, refer to Figure 1.

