### 2.4. Outcome Measures

#### 2.4.1. Primary Outcomes

The primary outcome of this study will be the change in daily steps from baseline to three months and six months. Daily steps will be assessed using the Xiaomi Mi Band 5 smartwatch, a reliable wearable activity tracker that has been validated in previous research [35,36,37]. Days with missing data, defined as days with fewer than 1000 steps, based on previous literature [38,39], will be excluded from the analysis [40,41] to ensure accurate and comprehensive data representation.

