#### 2.4.2. Secondary Outcomes

The secondary outcomes include changes in: (1) physical activity; (2) anthropometric measurements and body composition; (3) physical capacities; (4) well-being. In addition, psychological mediators will also be examined.

The following criteria will be used in order to measure the WISE program adherence [42]:Retention (completion): the participants following the WISE exercise videos and showing up to the follow-up measurements.Attendance: percentage of videos completed of the total of 50 videosDuration: adherence to a minimum of 20 min of exercise two times a week.Intensity: intensity levels of the sessions will be assessed at the end of each session using the modified Borg Scale, which measures perceived exertion [43].

These items will be measured through a weekly online exercise diary, where the participants will be asked if they completed both video sessions. They will also be asked about their perceived exertion after each session. This will allow us to assess whether they are following the 20 min of exercise two times a week rule, completing the video sessions, so we can see the number of videos completed at the end of the program.

Table 1 presents the assessment schedule, following the Standard Protocol Items: Recommendations for Interventional Trials (SPIRIT) schedule template. Table 5 provides an overview of all the outcome measures.

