## 3. Statistical Analyses Plan

All the statistical analysis will be performed using the SPSS version 24 Software (SPSS Inc., Chicago, IL, USA). If adherence issues occur, all analyses will be evaluated by intention-to-treat principles, with a level of significance of 0.05. Continuous outcomes will be presented using mean and standard deviation if they follow a normal distribution. On the other hand, count outcomes, such as WISE sessions completed, will be reported through the median and percentage of achievement. At the basal assessment, an independent-samples Student’s *t*-test will be performed to rule out differences between groups of age and height of participants.

In order to answer the first aim of this study, the changes in the adherence variables, such as daily steps, the Borg scale and the IPA questionnaire, will be analyzed by 1-within-subject factor multivariate analysis of variance (MANOVA). The Bonferroni adjustment will be used for post-hoc comparisons between the T0, T1 and T2 times assessments. On the other hand, the secondary outcomes of the study will be tested by 2-factor mixed MANOVA to analyze the effects of a within-subject factor (time assessment from T0 to T4), the between-subject factor (group) and their interaction. As mentioned above, Bonferroni adjustment will be used for times and groups comparisons. In addition, the same statistical test will be carried out considering the country of origin of the data as a covariate, and the findings will be reported according to their statistical significance. For all the statistical analyses, differences will be declared statistically significant if the *p*-value is less than 0.05. The exact *p*-value and 95% confidence interval will be reported.

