## 5. Conclusions

This study aims to investigate the effectiveness of an online HIIT program with nutritional plans and other health-related advice in improving exercise adherence and various health outcomes among sedentary young women. A significant contribution of this study is the development of guidelines to promote exercise engagement in this population.

We expect that the WISE program will improve the participants’ knowledge of physical activity, proper nutrition and healthy habits. The program’s physical activity component will involve monitoring the participants’ heart rate, number of steps and body composition, including fat percentage, visceral fat, water and muscle mass. The diet and healthy habits component will offer basic guidelines and advice on healthy eating, quality sleep and adequate water intake, all delivered via a mobile application.

However, the study design has some limitations, including the program’s duration of six consecutive months, which includes vacations and local holidays, as well as the challenge of ensuring that the participants adhere to the program, such as wearing the smartwatches. Depending on the results obtained, the WISE program may consider adjusting the sessions to be more individualized. Additionally, as noted by DiPietro et al. [63], it is important to acknowledge that the WHO recommendations used as a filter in this study are general guidelines for the population as a whole and may not be specifically tailored to certain subpopulations, such as sedentary young women. Finally, increasing the sample size will enable the development of a specification equation (via regression analysis) to determine the general health status of the women in each age group.

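### The primary outcome, daily steps, is given a model with time as its only factor, so no stated analysis compares steps between the randomised arms

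*Protocol article*

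**What the plan says.** Section 2.4.1 defines the endpoint: "The primary outcome of this study will be the change in daily steps from baseline to three months and six months". Table 5 lists daily step count alone under the primary outcome. Section 2.1 describes the design as a "three-center, randomized (1:1), controlled, parallel-group trial with a six-month intervention period".

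Section 3 then assigns models to outcomes. For the first aim, "daily steps, the Borg scale and the IPA questionnaire, will be analyzed by 1-within-subject factor multivariate analysis of variance (MANOVA"). The follow-up tests for that model are also confined to time: "The Bonferroni adjustment will be used for post-hoc comparisons between the T0, T1 and T2 times assessments". The next sentence is set up as a contrast: "the secondary outcomes of the study will be tested by 2-factor mixed MANOVA to analyze the effects of a within-subject factor", together with "the between-subject factor (group) and their interaction".

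Section 2.4.2 says how the Borg rating arises: "intensity levels of the sessions will be assessed at the end of each session using the modified Borg Scale". According to Table 4, the control group receives the video sessions only after the programme ends.

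**The concern.** The plan sets a one-factor model against a two-factor model and puts the primary outcome under the one without group. This is a stated choice, not a detail left to a fuller analysis plan. Read as written, the headline test asks whether steps changed between T0, T1 and T2. It does not ask whether they changed more with the programme than without it.

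Steps could move in both arms for reasons unrelated to the programme. All participants are enrolled because they report low activity (section 2.2.1), and all receive a tracker (section 2.2.2). The authors also list as a limitation a "duration of six consecutive months, which includes vacations and local holidays". Randomisation protects against such influences only if the arms are compared. Without that comparison the trial could report success when nothing but a common drift occurred, or miss a real difference when the arms move in opposite directions.

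**Working it through.** **1. The plan's own sample size.** Inputs from section 2.2.3: d = 0.50, taken from a meta-analytic effect against control groups; power 90%; two-sided alpha 0.05; 240 required; 20% dropout.
- Dropout step: 240 / 0.80 = 300, as stated.
- Two-group formula: n per arm = 2(1.96 + 1.2816)² / 0.5² = 84.06, rounded up to 85, or 170 in total. The stated 240 does not follow from this formula. That is a separate matter. What counts here is that the effect size is a between-group one.
- Power of a between-group test with 120 completers per arm: Φ(0.5 × √(120/2) − 1.96) = Φ(3.873 − 1.960) = Φ(1.913) = 0.97.

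The planned numbers are therefore enough for the comparison that is missing.

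**2. Whether any other sentence supplies a group comparison for steps.**
- Baseline t-tests: age and height only.
- Two-factor mixed MANOVA: secondary outcomes only. Steps is not listed as secondary in section 2.4.2 or Table 5.
- Bonferroni for comparisons of times and groups: follows the mixed MANOVA and needs a model that contains group.
- Re-analysis with country as covariate: repeats the same test and adds no group factor.

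None does. IPAQ, which is also a secondary outcome, does get a group comparison.

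**3. What a time-only test does under a common drift.** Assumptions: no programme effect; the same mean change in both arms; SD of change equal to 1 SD, which corresponds to a correlation of 0.5 between visits, since √(2(1 − 0.5)) = 1; two time points. The documents give no drift size, so a range is shown.

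P(significant) ≈ Φ(drift × √n − 1.96)

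| Common drift (SD) | Pooled, n = 240 | One arm, n = 120 |
|---|---|---|
| 0.1 | Φ(1.549 − 1.960) = 34% | Φ(1.095 − 1.960) = 19% |
| 0.2 | Φ(3.098 − 1.960) = 87% | Φ(2.191 − 1.960) = 59% |
| 0.3 | Φ(4.648 − 1.960) = 99.6% | Φ(3.286 − 1.960) = 91% |

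A simulation with 120 per arm and 20,000 repetitions agreed. At 0.2 and 0.3 SD the pooled time test was significant in 87% and 99.7% of trials, and the single-arm test in 59% and 91%. The between-group t-test was significant in 4.9% and 4.7%. A three-visit version (Hotelling test on the two changes, equal drift at T1 and T2, correlation 0.5, 240 pooled) gave 89% and 99.9%.

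**4. The opposite error.** With a true between-group difference of 0.5 SD made up of −0.25 SD in controls and +0.25 SD in the intervention arm, the pooled time test was significant in 4.5% of simulated trials and the between-group test in 97%.

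**5. Borg.** It is rated after video sessions, which begin after T0 and go only to the intervention arm during the trial. So it has no T0 value and no control values.

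**The case against.** The strongest reply is that the first aim is about adherence. The study aims open with adherence to the HIIT programme, section 3 calls these variables adherence variables, and a within-subject analysis of the intervention arm would suit that. This is fair for Borg. It does not rescue steps: the same aims paragraph makes change in daily steps the measure of effectiveness, and both arms wear the tracker.

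A reader might go further than the text allows in three ways.

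- *That steps, Borg and IPAQ form one response vector, so the primary model cannot be fitted.* The three are given as examples, and the text does not say that they are analysed together. Multivariate tests over time are also used for a single outcome. If they are one vector, a complete-case fit from T0 is impossible because of Borg, and an omnibus result would not be a test on steps. If each is analysed separately, that problem falls on Borg alone, and the missing group factor for steps remains.
- *That the authors will never compare steps between arms.* The design and sample-size sections suggest that they intend to. What stands is that no stated model does it.
- *That steps will in fact drift.* The documents give no size or direction. Selection is on self-reported activity, so regression to the mean in device steps is indirect. Holidays are named as a limitation only, and influences may offset one another.

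It is also fair that a time test which rejects under real drift makes no type I error about time. The error lies in attributing the drift to the programme.

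**Conclusion.** The point holds and should be corrected before analysis. Section 3 gives the sole primary outcome a time-only model and reserves group and group-by-time for the secondary outcomes. This conflicts with the randomised controlled design in section 2.1 and with the between-group effect size in section 2.2.3. The conclusion rests on the wording alone and needs no assumption about drift.

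The figures show what is at stake and do not forecast a result. They assume equal drift in both arms, an SD of change of 1, 240 completers in total and a simple two-time-point test. They also depend on whether the arms are pooled or only one is tested, which the plan does not say. Borg cannot be analysed from T0 on either reading. That the whole primary model cannot be fitted is true only if the three variables are meant as one response vector.

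**What to change.** Replace the first-aim sentences in section 3 so that:

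1. The primary analysis is the between-group difference in change in daily steps, with steps analysed alone.
2. The model contains group, time and group-by-time. The protocol's own two-factor mixed analysis would do. So would a linear mixed model that adds baseline steps and country.
3. The difference is reported with its 95% CI at three and at six months. Section 2.4.1 names both and ranks neither, so either one is declared primary or the two are adjusted for. With alpha halved for two comparisons, 90% power at d = 0.5 needs 200 in total by the same formula, still below the planned 240 completers.
4. Borg is reported descriptively in the intervention arm, and IPAQ stays with the secondary outcomes, where Table 5 places it.

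The cost is one paragraph of wording. No new data or participants are needed.

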## Abstract

Background: Physical inactivity is a serious public health problem for people of all ages and is currently the fourth highest global risk factor for mortality. The transition period from adolescence to adulthood coincides with a marked reduction in participation in physical activity, with more than 50% (and up to 80%) of young adults stopping physical activity. This decrease in physical activity is more evident in women than in men. Despite efforts, existing programs face challenges in effectively initiating and maintaining physical activity among individuals, particularly women, for extended durations. To address these limitations, the Women’s Involvement in Steady Exercise (WISE) randomized controlled trial (RCT) seeks to assess the efficacy of a digital high-intensity training intervention complemented by nutritional plans and other health-related advice. Methods: The study will be a three-center, randomized (1:1), controlled, parallel-group trial with a six-month intervention period. A total of 300 participants will be recruited at three study sites in Spain, Serbia and Italy. The participants will be randomized to one of the two groups and will follow a six-month program. The primary outcome of the study is the daily step count. Self-reported physical activity, the adherence to the exercise program, body composition, physical activity enjoyment, quality of sleep and physical capacities will also be evaluated.

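### Country is to enter the repeated-measures model as a covariate; taken literally as one numeric SPSS term, this makes the overall time test in the country-adjusted run depend on arbitrary country codes

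*Protocol article*

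**What the plan says.** Section 3 (Statistical Analyses Plan) names the software: "All the statistical analysis will be performed using the SPSS version 24 Software". It then sets out two models.

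- For the first aim, the adherence variables, daily steps among them, "will be analyzed by 1-within-subject factor multivariate analysis of variance (MANOVA"). Time is the only factor.
- For the secondary outcomes it plans a "2-factor mixed MANOVA to analyze the effects of a within-subject factor (time assessment from T0 to T4), the between-subject factor (group) and their interaction".

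For follow-up of the time effect, "The Bonferroni adjustment will be used for post-hoc comparisons between the T0, T1 and T2 times assessments". An additional analysis follows, in which "the same statistical test will be carried out considering the country of origin of the data as a covariate". On what then reaches the report, the plan says that "the findings will be reported according to their statistical significance".

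There are three countries (Abstract: "A total of 300 participants will be recruited at three study sites in Spain, Serbia and Italy"). Section 2.2.2 sets 100 women per country and 150 per group. The article does not say how country is coded, whether it is centred, or whether the additional run repeats the mixed model only or both models.

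**The concern.** The same paragraph calls time and group factors and country a covariate. A repeated-measures GLM treats the two differently: a factor gets a separate level for each category, while a covariate is read as a number and gets one slope. Country is a label, so a slope across its codes has no meaning.

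The effect on the time test is less obvious. With a covariate in the model, the omnibus time test is a test of the intercept in the regression of the change scores on the between-subject terms, which is the change at covariate value 0. Unless the covariate is centred, that is not the average change over the three countries. The test can then lose power, reject when the average change is zero, or give a different answer when the codes are reordered. It can also disagree with the pairwise time comparisons, which are evaluated at the covariate mean and so describe another quantity.

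Time is a tested effect for every secondary outcome, and it is the only effect in the daily-steps model if the additional run extends to that model.

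**Working it through.** The article gives no figure on this point, so there is none to reproduce.

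**Inputs from the protocol.** Three countries with 100 women each; two groups of 150; three visits (T0, T1 and T2, section 2.3.1); significance level 0.05.

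**Assumptions, not in the protocol.** Country codes 1/2/3, 0/1/2 or -1/0/1; outcome SD 1; within-person correlation 0.5; a change that reaches size *a* (in SD) at T2 and half of that at T1; no dropout; group entered in centred form.

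**Step 1: variance of the tested time effect.** For an intercept estimated beside a covariate *x*, the variance relative to that of the mean change is 1 + mean(x)² / var(x). With equal countries and consecutive codes, var(x) = 2/3.

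| Codes | Mean | Variance ratio | SE ratio |
|---|---|---|---|
| 1/2/3 | 2 | 1 + 4/(2/3) = 7.0 | 2.65 |
| 0/1/2 | 1 | 1 + 1/(2/3) = 2.5 | 1.58 |
| -1/0/1 | 0 | 1 + 0 = 1.0 | 1.00 |

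**Step 2: power when all countries change alike.** The change scores (T1-T0, T2-T0) each have variance 2 - 2(0.5) = 1 and covariance 0.5. For the change pattern (a/2, a), the quadratic form with the inverse covariance is (a²/4 + a² - a²/2)/0.75 = a². The noncentrality of the omnibus F test (2 numerator df) is therefore 300a²/v, where v is the variance ratio. With a = 0.3:

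- three-level factor, v = 1: 300 × 0.09 = 27, power 0.998;
- codes 1/2/3, v = 7: 27/7 = 3.86, power 0.40 (simulation 0.39 to 0.40, 2,000 runs);
- codes 0/1/2, v = 2.5: 27/2.5 = 10.8, power 0.84 (simulation 0.84).

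**Step 3: countries that differ, average change zero.** Take true T2 changes of -0.3, 0 and +0.3. With codes 1/2/3 in that order, the line falls by 0.3 per code going down and reaches -0.6 at code 0. Noncentrality is 300 × 0.36/7 = 15.4, and the test rejects with probability 0.95 (simulation 0.945). With a factor, simulated rejection is 0.056.

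**Step 4: code order.** Take true changes of 0.5, 0.3 and 0.1 (average 0.3). Coded 1/2/3, the fitted value at 0 is 0.7, noncentrality 300 × 0.49/7 = 21.0, and simulated rejection is 0.99. Coded 3/2/1, the fitted value at 0 is -0.1, noncentrality 300 × 0.01/7 = 0.43, and simulated rejection is 0.07. With a factor it is 0.998.

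**Step 5: what is not affected.**

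- *Group-by-time, size.* Simulated rejection without a group effect is 0.046 to 0.050 across the codings tried, against 0.049 with a factor.
- *Group-by-time, power.* With a group effect of 0.3 SD, power is 0.658 with a factor. It is 0.651 to 0.658 with numeric codes when countries change alike or by 0.5/0.3/0.1. If one country differs sharply (0.9/0/0), it is 0.59 to 0.64.
- *Bonferroni time comparisons.* A fitted line passes through the mean of *x* and the mean change, so estimates taken at the covariate mean equal the overall means whatever the codes.

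**The case against.** The strongest objection is that the plan does not state the error. It gives no codes and no linear term, and trial reports often use the word covariate for any adjustment variable, categorical ones included. How a three-level variable is parameterised is also something a condensed article may leave to a fuller document. This stands in part. The consequence is conditional, and a reader who infers that the time effect will be tested at a country code that does not exist goes beyond the text: with 0/1/2 or -1/0/1, code 0 is a real country. But the paragraph itself separates factors from a covariate and names the software, so the literal reading is open, and following it gives a worse analysis. That is more than an omitted detail.

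Second, the run is additional. The planned main models contain no country term, and the wording on repeating the test follows directly after the mixed model, so it may not cover daily steps. This stands.

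Third, the randomised comparison is essentially untouched, and the pairwise time estimates are not distorted. This stands too. It would be wrong to infer that the trial's treatment comparison is biased, or that the omnibus test reverses sign, since a test over three visits has no sign.

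**Conclusion.** The point holds as a conditional one. If country is entered as a single uncentred numeric covariate, the omnibus time test in the country-adjusted run refers to code 0 and depends on an arbitrary choice of labels. With equal countries, the variance ratio is 7 for codes 1/2/3, 2.5 for 0/1/2 and 1.0 for -1/0/1, so the damage ranges from large to none according to a choice that the article does not record. The rejection rates above also rest on an assumed SD, correlation and pattern of country changes; they illustrate the mechanism and do not predict this trial's results.

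The defect does not reach the main models, the size of the group-by-time test or the Bonferroni time estimates. It is most serious if the additional run includes the time-only model for daily steps, because time is then the only effect tested. The statement that these findings will be reported according to significance means that a coding-dependent p-value could influence what is published.

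**What to change.** In section 3, say that country enters as a between-subject fixed factor with three levels (2 df) in place of a covariate. Two centred indicator variables serve equally well; uncentred 0/1 indicators do not, because the time test would then refer to the reference country alone. With the factor, the time effect is the average over the three countries, and the group comparison is adjusted for all between-country differences in place of a linear part of them. The same sentence should say whether the additional run covers the mixed model only or the daily-steps model as well. The cost is a change of wording before analysis and one extra degree of freedom among about 300 women.

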#### 2.2.2. Recruitment

A total of 300 participants (150 per group) will be recruited between the three countries. Each country will recruit 100 young women for the study. Dissemination of the project will be conducted via email and posters in close contact with universities, schools and local authorities. Through the information of the posters and emails, interested participants will contact the investigators and will be informed about the study in order to decide if they finally want to participate. Those willing to participate will be summoned for a personal interview to check if they meet the inclusion criteria. Participants who meet the inclusion criteria will be invited to participate in the study and will sign a written consent form before being included in the study. At the start of the study, a wearable device (Xiaomi Mi Band 5) will be distributed to all participants.

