#### 2.2.3. Sample Size and Power Analysis

Sample size estimations were derived from the primary outcome measure of daily step count, measured using the Xiaomi Mi Band 5. A priori sample size calculation was conducted based on a previous meta-analysis [33], which reported an effect size of d = 0.51 (95% CI 0.12 to 0.91, I² = 90%), compared with control groups, for physical activity interventions that included wearables and smartphone apps. Our sample size estimation was based on an intermediate effect size of d = 0.50.

To detect a difference equivalent to an effect size of 0.5 on the primary outcome with 90% power and a two-sided type I error of 0.05, a sample size of 240 is required. Specifically, assuming that the statistical unit is an individual day and considering an intraclass correlation coefficient of 0.5 to account for interindividual and intraindividual variability, a total of 2002 individual days per group (equivalent to 22 participants per group) are necessary. We suggest including a total of 300 participants (150 per group) in order to protect against a potential dropout of 20%, inherent to such a trial.

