#### 2.2.4. Randomization, Allocation and Blinding

After the first experimental visit (T0), the participants will be randomized using a computer-generated randomization list into one of the two conditions with a 1:1 allocation. The allocation will be transmitted using numbered (0 = control/1 = Intervention), opaque and sealed envelopes, which will be given to the young women and then registered by the data collectors. The assessors will be blinded to the treatment allocation, although double blinding is not applicable in interventions of this nature as it is impossible to conceal the allocation from the participants. The participants will be instructed not to reveal their allocation to the assessors to ensure unbiased assessment.

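### The plan runs the test without and with country, names neither as the main analysis, and ties reporting to statistical significance

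*Protocol article*

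**What the plan says.** Section 3 (Statistical Analyses Plan) of the protocol article assigns two models. For the first aim, the adherence variables, daily steps among them, get a model with one within-subject factor. For the rest, "the secondary outcomes of the study will be tested by 2-factor mixed MANOVA to analyze the effects of a within-subject factor", together with group and the interaction.

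After a remark on Bonferroni adjustment, the section continues: "In addition, the same statistical test will be carried out considering the country of origin of the data as a covariate". The same sentence ends by saying that the findings will be reported according to their significance (the full clause is "considering the country of origin of the data as a covariate, and the findings will be reported according to their statistical significance"). The paragraph then sets the threshold, "differences will be declared statistically significant if the *p*-value is less than 0.05", and promises exact p-values and 95% confidence intervals.

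Country is part of the design. Section 2.2.2 states: "Each country will recruit 100 young women for the study". Section 3 mentions country only in the sentence at issue.

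**The concern.** Two versions of a test are planned on the same data. A reader of the eventual report needs to know beforehand which one carries the conclusion. The article does not say, and the only criterion it attaches to reporting is statistical significance.

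The clause can steer the choice of model in two ways:

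- **Significance of the group or time effects.** The version with the more favourable p-value can be presented. The error rate of that procedure is above the nominal 5%, and the confidence interval shown belongs to a model selected for its result.
- **Significance of the country term.** A preliminary test on the trial's own data selects the model. The error rate for group is then largely preserved, but the presented analysis is still decided after the data are seen.

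On either reading, a later reader could not tell whether the published model was the intended one.

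**Working it through.** The article gives no figure for this rule, so there is none to reproduce. The check asks how much the error rate could move.

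**Inputs from the article.** Three countries with 100 women each (section 2.2.2). 300 women, 150 per group, with 240 as the required number before the dropout allowance (section 2.2.3). Two-sided alpha of 0.05 (section 2.2.3), with the same 0.05 threshold for all analyses (section 3).

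**Assumption.** The share of variance in the analysed quantity that country explains, R², is not given. It is varied from 0 to 30%.

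**Bounds.** One fixed test gives 0.05. Two independent tests would give 1 − 0.95² = 0.0975. The two versions here are strongly correlated, so the true value lies between.

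**Simulation.** No group effect, one endpoint, and a two-group linear model fitted without and with country as a three-level factor; 10,000 trials per setting. This is a simplified stand-in for the MANOVA. *Smaller p* means that the version with the smaller p-value is presented. *Country term decides* means that the adjusted model is used only if country has p < 0.05. Each cell gives type I error at N = 240 / N = 300.

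| R² | Smaller p, unstratified | Smaller p, stratified by country | Country term decides, unstratified |
|---|---|---|---|
| 0 | 0.053 / 0.052 | 0.051 / 0.051 | 0.050 / 0.049 |
| 5% | 0.060 / 0.058 | 0.052 / 0.047 | 0.050 / 0.049 |
| 10% | 0.063 / 0.065 | 0.050 / 0.051 | 0.048 / 0.050 |
| 20% | 0.072 / 0.073 | 0.053 / 0.052 | 0.052 / 0.051 |
| 30% | 0.075 / 0.074 | 0.052 / 0.049 | 0.050 / 0.050 |

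The simulation standard error is √(0.05 × 0.95 / 10,000) ≈ 0.002 near 5%. The country-adjusted model, fixed in advance, stayed between 0.047 and 0.053 throughout. Under unstratified allocation the two versions disagreed on significance in about 0.6% of null trials at R² = 0 and about 5% at R² = 30%.

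**Closed-form cross-check.** Under unstratified allocation, the unadjusted test statistic is approximately √(1 − R²) times the adjusted one plus an independent part from chance country imbalance. The two statistics therefore correlate at about √(1 − R²). The bivariate normal probability that at least one exceeds 1.96 in absolute value is:

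- R² = 5%: correlation 0.975, probability 0.060
- R² = 10%: correlation 0.949, probability 0.065
- R² = 20%: correlation 0.894, probability 0.071
- R² = 30%: correlation 0.837, probability 0.076

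This agrees with the simulation.

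**Change scores.** The outcomes are described as changes (sections 2.4.1 and 2.4.2). If a country difference is constant over time, subtraction removes it and the first row of the table applies. A simulation of a baseline-to-follow-up change (assumed within-person correlation 0.5, constant country effect, unstratified 150:150) gave 5.2%, 5.4% and 5.4% when country explains 0%, 10% and 30% of the cross-sectional variance. The higher values in the table therefore need country to explain 5% to 30% of the variance in the change itself.

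**The case against.** The strongest defence is that the clause only means results will be described as significant or not. The country run is introduced as an addition, which suggests a supplementary role, and the paragraph promises exact p-values and confidence intervals. This has some force: the wording does not prove that a p-value will choose the model, so a reader who infers a declared policy of selective reporting goes beyond the text. The defence does not remove the point. The threshold for declaring significance is set in the very next sentence, so on this reading the clause would be redundant. The promise of exact p-values also does not commit the authors to showing both versions.

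Three further inferences are tempting and not supported:

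- **That every test is affected, including the primary outcome.** The sentence refers to one test and directly follows the mixed MANOVA for the secondary outcomes. Extension to daily steps is possible but not stated.
- **That allocation ignores country and sites will be unbalanced.** Section 2.2.4 says participants are "randomized using a computer-generated randomization list into one of the two conditions with a 1:1 allocation" and is silent on stratification. A condensed article commonly leaves that to the full protocol. The unstratified figures above are therefore conditional.
- **That country would enter as a numeric code with a forced linear trend.** Calling it a covariate does not establish this, because the word is often used for any adjustment variable. How country is coded can properly be left to the analysis plan.

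The objection that the inflation is small also stands, and it limits the weight of the point.

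**Conclusion.** The point holds as a defect of pre-specification. Section 3 plans two versions of a test, designates neither as the main one, and leaves the choice open to a p-value whose identity is not stated. This is certain for the secondary-outcome mixed MANOVA and unclear for daily steps.

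The effect on type I error is modest. It is about 6% to 7.5% per endpoint instead of 5%, and only if three things hold together: the more favourable version is presented, allocation is not stratified by country, and country explains 5% to 30% of the variance in the analysed quantity. If any one of them fails, the error rate stays close to 5%. The main reason to act is that the presented model should be known before the data are seen. The change should be made, but the trial's validity does not turn on it.

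**What to change.** In section 3, name one model per outcome, with country as a three-level factor, and state that it is reported whatever its p-value. State that the version without country is always shown beside it as a labelled supplement. Say explicitly whether this applies to daily steps as well as to the secondary outcomes. Delete the clause that makes reporting depend on statistical significance.

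The cost is one rewritten sentence and two degrees of freedom (3 − 1 = 2), negligible with 240 to 300 women. No change to recruitment or data collection is needed. The amendment can still be made after recruitment has begun, provided it is dated before any unblinded analysis.
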